**Methods:**

This cohort study is monocentric and prospective. The primary objectives are to determine the risk factor of sarcopenia prevalence and to study the relationship between ADT and sarcopenia incidence, in patients 70 years and older with histologically proven localized or locally advanced prostate cancer, addressed to a geriatrician (G8 score ≤14) for comprehensive geriatric assessment (CGA) in Marseille University Hospital. Secondary objectives encompass, measurement of sarcopenia clinical criteria along prostate oncological treatment; evaluation of the quality of life of patients with sarcopenia; evaluation of the impact of socio-behavioral and anthropological factors on sarcopenia evolution and incidence; finally the evaluation of the impact of ADT exposure on sarcopenia. Sarcopenia prevalence was estimated to be between 20 and 30%, therefore the study will enroll 200 patients.

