### Recruitment and follow-up

#### Screening and enrollment - T0

Eligible patients will be identified by the radiotherapist and/or the urologist and/or the geriatrician. Patient over 70 years old screened with a G8 score ≤ 14/17 will be addressed to the geriatrician and benefit from full CGA and sarcopenia assessment: sarcopenia risk will be evaluated using the SARC-F questionnaire (Strength, Assistance walking, Rise from a chair, Climb stairs, and Falls questionnaire). Muscle strength will be assessed for patient at risk of sarcopenia (impaired SARC-F). For patient with probable sarcopenia (impaired muscle strength), sarcopenia diagnosis will be confirmed by measuring the skeletal muscle index (SMI). The severity of sarcopenia will also be evaluated.

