#### Follow-up – T1

A year after standard treatment completion, patient will once again benefit from CGA and sarcopenia assessment as described for T0.

Total duration of study will be 48 months, recruitment period will be 24 months and patient follow-up period, 12 months. A year after ADT end, patient will be contacted either by the geriatrician or the study coordinator to schedule the follow-up (T1). The study procedure and data collection are detailed in Table 1.

**Table 1 Tab1:** HoSAGE Study schedule of activities and procedures

	T0	Treatment phase	T1
Oncologist consultation	X	X	
Diagnosis	X		
G8 score ≤14	X		
Geriatrician consultation	X		X
Enlighten consent	X		X
Enrollment	X		X
CGA	X		X
Demographic information	X		X
Social isolation	X		X
Cognitive status (MMSE and clock drawing test)	X		X
Mood status (GDS)	X		X
Autonomy (ADL and IADL Score)	X		X
Nutritional status (BMI, MNA score and Albumin)	X		X
Mobility (OLGT, Gait speed)	X		X
Sarcopenia screening (SARC-F, Handgrip test and chair stand test)	X		X
If Sarcopenia risk suspected (SARC-F≥4/10), and Muscle strength is impaired, SMI will be measured by (DXA)^a^	X^a^		X^a^
Radiotherapy treatment (dates, dose delivered and number of fractions)		X	
Androgen deprivation therapy (dates, dose delivered, frequency, adverse events)		X	

^a^DXA assessment performed only if SARC-F score is ≥4/10 and muscle strength is impaired (either handgrip strength under 27 kg for men and 16kg for women or five chair stand test is performed in more than 15 seconds)

*CGA: Comprehensive Geriatric Assessment; MMSE: Mini Mental State Examination; GDS: Geriatric Depression Scale; ADL: Activity of Daily Living; IADL: Instrumental Activity of Daily Living; BMI: Body Mass Index; MNA: Mini Nutritional Assessment; OLGT: One Leg Balance Test; SARC-F: Strength, Assistance walking, Rise from a chair, Climb stairs, and Falls; SMI: Skeletal Muscle Index (appendicular muscular mass/seize*^*2*^*); DXA: Dual-energy X-ray*

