### Endpoints/Evaluation criteria

#### Primary endpoint

The primary endpoint is:The evaluation of sarcopenia prevalence for patients 70 years and older with localized or locally advanced prostate cancer before treatment initiation.

The geriatrician will screen for suspicion of sarcopenia using the SARC-F questionnaire and muscle strength assessment as recommended by the EWGSOP2 guidelines [10]. Patient whose SARC-F score is superior or equal to four out of ten are at risk of sarcopenia and will undergo muscle strength assessment. Patient with impaired muscle strength (either handgrip strength under 27 kg for men and 16kg for women or five chair stand in more than 15 seconds) are considered with probable sarcopenia [10]. To ascertain sarcopenia diagnosis, SMI will be estimated using the Appendicular Skeletal Muscle Mass (ASMM) measured with dual-energy X-ray absorptiometry (DXA) [17], adjusted for body size (ASMM/height^2^). Chosen cut-off point for low SMI indicating sarcopenia diagnosis as per EWGSOP2 guidelines is <7.0 kg/m2 [10]. Sarcopenia severity will be evaluated using Timed up and Go test and Gait speed assessment.

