#### Secondary endpoints

The secondary endpoints are:The evaluation of sarcopenia incidence in patients 70 years and older with localized or locally advanced prostate cancer a year after the end of ADT. Sarcopenia assessment will be lead at enrollment and a year after ADT end.Evaluate the evolution of the physical performances by the measurement of mobility (Timed Up and Go test, gait speed and chair stand test) at enrollment and after ADT in patients 70 years and older with localized or locally advanced prostate.Evaluate quality of life (QoL) evolution before and after ADT for patient 70 years and older with localized or locally advanced prostate with or without sarcopenia. QoL will be evaluated using EORTC QLQ-c30 questionnaires and ELD-14 module at enrollment and a year after ADT end.Evaluate impact of socio-behavioral, anthropological and geriatric factors on sarcopenia prevalence for patients 70 years and older with localized or locally advanced prostate and on its incidence after ADT. Geriatric factors such as Autonomy (score <6 on Activity of Daily Living (ADL) Scale and score <4 on Instrumental Activity of Daily Living (IADL) scale) [18], nutrition (Weight, Body Mass index (BMI), Albumin, Mini Nutritional Assessment (MNA) )[19]., cognitive status (Mini Mental State Examination (MMSE)) [16], mood (Geriatric Depression Scale (GDS)) [20], polypharmacy, and comorbidities will be assessed by CGA. Demographic information such as age, gender, presence of a caregiver, urban or countryside way of living and physical activity (number of days when patient exercise an hour at least).Evaluate impact of ADT of patients 70 years and older with localized or locally advanced prostate on sarcopenia. Oncological data such as cancer stage and anatomy; testosterone and PSA levels at enrollment and a year after ADT end; treatment protocol for radiotherapy and ADT will also be collected.

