### Statistical considerations

#### Sample size, power, and statistical methods

Under the assumption that the prevalence of sarcopenia in older patients with prostate cancer before initiation of treatment with ADT is between 20 to 30%, according to one of the rare studies published on the subject [21], a sample size of 200 subjects allows an estimation with a width of two-sided 95% confidence interval between 0,115 to 0.131. Previous feasibility analysis showed current collaboration between urologist, radiotherapist and geriatrician should allow enrollment of the adequate number of patients during the trial period.

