#### Data analysis

The data will be analyzed using SPSS version 17.0 software. Method and analysis will be based on the Consolidated Standards Of Reporting Trials Statement (CONSORT) (http://www.consort-statement.org/consort-statement/). The patients who would be inappropriately included despite providing consent and patients who removed their consent to participate won’t be included in the final analysis. The full population (including all subjects who will be enrolled and will be at least evaluated at T0) will be included in the analysis of primary endpoint. The normality of the parameters will be estimated using frequency histograms and the Shapiro test; the baseline parameters will be presented according to the timeline of assessments: ‘Enrollment – T0’ and ‘A year after ADT end – T1’.

The SMI under 7 kg/m^2^ at enrollment and /or a year after ADT end is considered as a proven sarcopenia diagnosis. Along with incidence of sarcopenia, we will monitor evolution of SMI and/or of physical performances (handgrip strength and/or chair stand test) for diagnosed sarcopenic patient. Only patients with probable sarcopenia (SARC-F score ≥4/10 and then muscle strength impairment), will benefit from a DXA exam [10, 22, 23]. To evaluate incidence, enrollment (T0) will be considered as baseline and compared to T1 data. Changes between initial SMI and/or handgrip strength and/or chair stand test will be compared between the two groups, and the analysis of variance for repeated measurements will be performed to compare the changes in the scores over time between the 2 groups. Multivariate analysis using linear regression models will be performed to determine the association between our analyzed variables and sarcopenia occurrence. Variables relevant to the models will be selected based on their clinical significance (two-tailed with 5% significance level). The secondary endpoints will be compared for all the patients between the 2 assessments (Chi2 test or Fisher’s exact test for categorical variables and Student’s t test for continuous variables).

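### Confirmed sarcopenia requires SARC-F ≥4 first, so the risk-factor model can credit to muscle a factor that only raises SARC-F

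*Protocol article*

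**What the plan says.** The abstract (Methods) states: "The primary objectives are to determine the risk factor of sarcopenia prevalence". In the body, prevalence is the primary endpoint, and the factor question is one of the Secondary endpoints: "Evaluate impact of socio-behavioral, anthropological and geriatric factors on sarcopenia prevalence for patients 70 years and older", with incidence after ADT added. The factors listed there include autonomy, nutrition, cognition, mood, polypharmacy, comorbidities and presence of a caregiver.

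The route to diagnosis is stepwise. Under Primary endpoint: "Patient whose SARC-F score is superior or equal to four out of ten are at risk of sarcopenia and will undergo muscle strength assessment". Footnote a of Table 1 adds: "DXA assessment performed only if SARC-F score is ≥4/10 and muscle strength is impaired". Screening and enrollment – T0 and Data analysis give the same DXA restriction, and Data analysis treats SMI under 7 kg/m² as the proven diagnosis. The T0 section describes the first step as the "SARC-F questionnaire (Strength, Assistance walking, Rise from a chair, Climb stairs, and Falls questionnaire".

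The planned model is in Data analysis: "Multivariate analysis using linear regression models will be performed to determine the association between our analyzed variables and sarcopenia occurrence". No DXA in men with SARC-F below 4, and no correction for the stepwise route, is described.

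**The concern.** A man with SARC-F below 4 has no SMI and cannot be a case at T0 or T1, whatever his muscle. SARC-F asks about walking assistance, rising, stairs and falls. Low mood, poor cognition or having a caregiver could plausibly shift those answers without changing strength or muscle mass. Among men with truly low strength and low SMI, carriers of such a factor would then be found more often than non-carriers.

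That is differential under-detection, and it distorts the association itself. Renaming the prevalence as screen-detected describes the level honestly but leaves the factor estimates unchanged. Adjusting for other covariates does not recover SMI in men who were never scanned. The abstract's Discussion says the results should inform a prevention plan, so it matters whether a reported factor lowers muscle or merely raises SARC-F.

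**Working it through.** **The plan's own figure.** For "a sample size of 200 subjects allows an estimation with a width of two-sided 95% confidence interval between 0,115 to 0.131", the exact Clopper-Pearson interval with n = 200 has width 0.1153 at 20% and 0.1313 at 30%. The stated figure reproduces and is not in dispute.

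**Inputs from the protocol.** n = 200; two-sided 5% level; the assumption that "the prevalence of sarcopenia in older patients with prostate cancer before initiation of treatment with ADT is between 20 to 30" per cent.

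**Inputs assumed, because the protocol does not give them.** 40% of men carry the factor. The proportion π with low strength and low SMI is the same with and without the factor (true OR 1). The sensitivity s is the chance of SARC-F ≥4 among men with low strength and low SMI: s0 without the factor, s1 with it. Using overall SARC-F rates for s0 and s1 assumes that SARC-F is independent of muscle status; this is relaxed below.

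**Formulas.** P(confirmed) = π × s. With p0 = π·s0 and p1 = π·s1, apparent OR = [p1/(1−p1)] / [p0/(1−p0)]. The significance rate is the share of simulated cohorts of 200 in which a two-sided 5% Wald test of the log OR rejects.

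| True π | s0 v s1 | Confirmed p0 v p1 | Apparent OR | Significant |
|---|---|---|---|---|
| 20% | 0.40 v 0.70 | 8.0% v 14.0% | 1.87 | 26% |
| 30% | 0.40 v 0.70 | 12.0% v 21.0% | 1.95 | 40% |
| 20% | 0.50 v 0.65 | 10.0% v 13.0% | 1.34 | 10% |
| 30% | 0.50 v 0.65 | 15.0% v 19.5% | 1.37 | 13% |
| 20% | 0.95 v 0.98 | 19.0% v 19.6% | 1.04 | 5% |
| 30% | 0.95 v 0.98 | 28.5% v 29.4% | 1.04 | 5% |
| 45% | 0.40 v 0.70 | 18.0% v 31.5% | 2.09 | 59% |

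Worked line: at π = 0.30, (0.21/0.79)/(0.12/0.88) = 0.2658/0.1364 = 1.95.

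**Which π applies.** If 20–30% is the true rate, the 0.40 v 0.70 case yields a confirmed prevalence of 0.6×0.08 + 0.4×0.14 = 10.4% at π = 20%, and 0.6×0.12 + 0.4×0.21 = 15.6% at π = 30%. If 20–30% is the rate after the SARC-F step, the true rate must be higher: π = 45% gives 0.6×0.18 + 0.4×0.315 = 23.4%. The protocol does not say which is meant.

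**If SARC-F tracks muscle.** Take normal latent scores with a correlation of 0.6 in size between SARC-F and muscle deficit, and keep the overall SARC-F ≥4 rates at 40% and 70%. Sensitivity among affected men becomes about 0.724 v 0.936 at π = 25%. Confirmed risk is then 18.1% v 23.4%, and OR = (0.234/0.766)/(0.181/0.819) = 1.4. At π = 45%, sensitivity is about 0.620 v 0.887, confirmed risk 27.9% v 39.9%, and OR = (0.399/0.601)/(0.279/0.721) = 1.7.

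**Linear model, as the plan names.** A separate simulation used a linear-model t test on the binary diagnosis, with 50% exposed and true prevalence about 28%. A factor shifting SARC-F by 0.3, 0.5 or 1.0 SD was significant in 8–9%, 14–18% and 26–40% of studies. With strength and SMI known in every man, the rate was about 5%.

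**The case against.** A reader might infer that the analysis will report factors with no effect on muscle as risk factors. The documents do not support that certainty. The SARC-F step changes the result only among men who would also fail strength and SMI. Every confirmed case has measured low strength and low SMI, so nobody with normal muscle is falsely diagnosed. With sensitivity near 1 in both groups there is no inflation, and the protocol gives no sensitivity. The 59% figure needs both a 45% true rate and a SARC-F unrelated to muscle, although strength is one of its items.

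The comparison of confirmed cases with all other men is also an inference. Data analysis assigns the full population only to the primary endpoint and leaves the comparator of the factor model open. The example factors are plausible rather than shown; the Discussion itself lists disease, inactivity and nutrition disorders as causes of secondary sarcopenia, so comorbidities may well act on muscle. Risk factors are a primary objective only in the abstract.

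All of this stands, and it limits certainty and size. It does not remove the mechanism: the restriction of DXA is stated consistently, nothing described offsets it, and a later analysis plan cannot recover SMI in men who were not scanned.

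**Conclusion.** The concern holds in a bounded form. If confirmed cases are compared with all other men, the model can report biased associations, with an inflated false-positive risk, for factors that raise SARC-F among men who already have low strength and low SMI. At 20–30% true prevalence, for a factor with no effect on muscle, nominal significance runs from about 5% (sensitivities near 1) to 26–40% (0.40 v 0.70), with apparent OR from 1.04 to about 1.9. The OR of 2.1 and the 59% rate apply only at 45% true prevalence. If SARC-F correlates with muscle at 0.6, the 40% v 70% case falls to an OR of about 1.4–1.7. All these figures rest on assumed sensitivities and on 40% of men carrying the factor. The point should be addressed, but the protocol cannot settle how large the bias will be.

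**What to change.** 1. Reconcile who has strength measured. Table 1 lists handgrip and chair stand alongside SARC-F for all patients, and Secondary endpoints has chair stand at enrollment without a SARC-F condition. Screening and enrollment – T0 and Primary endpoint reserve strength assessment for men with SARC-F ≥4. Step 2 works only if strength is recorded in every man.

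2. In Secondary endpoints and Data analysis, add a factor model in all men whose outcome does not pass through SARC-F: impaired strength by the protocol's own cut-offs, or continuous handgrip and chair-stand time. Base statements about muscle risk factors on it.

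3. Keep the confirmed-sarcopenia model, state its comparator, and label it as factors of screen-detected sarcopenia. Do not read a factor as acting on muscle unless the strength model agrees.

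4. Treat any low-SMI model among scanned men as exploratory, because conditioning on SARC-F can itself bias it.

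Cost: if strength is recorded in every man as Table 1 lists, this is analysis wording only. If the SARC-F restriction governs, the model would need handgrip and chair stand recorded in men below 4 as well. In either case the risk-factor conclusion would rest on strength rather than on DXA-confirmed sarcopenia.

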### Statistical considerations

#### Sample size, power, and statistical methods

Under the assumption that the prevalence of sarcopenia in older patients with prostate cancer before initiation of treatment with ADT is between 20 to 30%, according to one of the rare studies published on the subject [21], a sample size of 200 subjects allows an estimation with a width of two-sided 95% confidence interval between 0,115 to 0.131. Previous feasibility analysis showed current collaboration between urologist, radiotherapist and geriatrician should allow enrollment of the adequate number of patients during the trial period.

#### Data analysis

The data will be analyzed using SPSS version 17.0 software. Method and analysis will be based on the Consolidated Standards Of Reporting Trials Statement (CONSORT) (http://www.consort-statement.org/consort-statement/). The patients who would be inappropriately included despite providing consent and patients who removed their consent to participate won’t be included in the final analysis. The full population (including all subjects who will be enrolled and will be at least evaluated at T0) will be included in the analysis of primary endpoint. The normality of the parameters will be estimated using frequency histograms and the Shapiro test; the baseline parameters will be presented according to the timeline of assessments: ‘Enrollment – T0’ and ‘A year after ADT end – T1’.

The SMI under 7 kg/m^2^ at enrollment and /or a year after ADT end is considered as a proven sarcopenia diagnosis. Along with incidence of sarcopenia, we will monitor evolution of SMI and/or of physical performances (handgrip strength and/or chair stand test) for diagnosed sarcopenic patient. Only patients with probable sarcopenia (SARC-F score ≥4/10 and then muscle strength impairment), will benefit from a DXA exam [10, 22, 23]. To evaluate incidence, enrollment (T0) will be considered as baseline and compared to T1 data. Changes between initial SMI and/or handgrip strength and/or chair stand test will be compared between the two groups, and the analysis of variance for repeated measurements will be performed to compare the changes in the scores over time between the 2 groups. Multivariate analysis using linear regression models will be performed to determine the association between our analyzed variables and sarcopenia occurrence. Variables relevant to the models will be selected based on their clinical significance (two-tailed with 5% significance level). The secondary endpoints will be compared for all the patients between the 2 assessments (Chi2 test or Fisher’s exact test for categorical variables and Student’s t test for continuous variables).

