## Discussion

Sarcopenia is an independent risk factor for adverse events as falls, increased hospital length of stay or readmission and death [24]. Prevalence of sarcopenia in the community was 1-33% with higher prevalence in older or acutely ill patients treated in care facilities. European Working Group on Sarcopenia in Older People (EWGSOP), discriminates two types of sarcopenia: primary, when non other cause than old age can be identified; secondary to physical inactivity (bed rest, immobility, sedentary lifestyle), to disease (like organ deficiency, inflammatory diseases, endocrinopathies or cancer) or to nutrition disorders (low protein or energy intakes, micronutrient deficiency …) [9].

Older patients are particularly at risk of sarcopenia as muscle mass decrease with age [11] and that protein-energy malnutrition is common in this age group [25].

Likewise patients with cancer often suffer malnutrition as a result of metabolic changes, mechanical blockages or abnormalities, side effects of treatment or psychosocial issues [26]. Even though malnutrition is less present in prostate cancer [27], androgen deprivation treatment leads to hypogonadism causing undesirable changes in lipid, glucose, muscle or bone metabolism leading to accelerated bone loss, osteoporosis and increased fracture risks [7, 28]. In a preliminary study we showed that muscle disorders were present before initiation of ADT in older patients with prostate cancer and an increased risk of falls at the end of ADT [29].

The aim of the HoSAGE study protocol is to evaluate the actual prevalence of sarcopenia in intermediate to high risk prostate cancer patients over 70 years old, and the incidence on sarcopenia in this population following ADT associated to radiotherapy. Using the most recent screening tool to detect sarcopenia (SARC-F) [10], the results of this study may lead to increment ADT with sarcopenia preventions programs.

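### DXA is re-triggered by SARC-F at each visit and T0 is compared with T1 for all patients, so men already sarcopenic but unscanned at T0 can be counted as incident cases; the net direction of bias is unknown

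*Protocol article*

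**What the plan says.** The Protocol article limits DXA to a subset of men. The footnote to Table 1, attached to both the T0 and the T1 columns, reads "DXA assessment performed only if SARC-F score is ≥4/10 and muscle strength is impaired". The Data analysis section repeats it: "Only patients with probable sarcopenia (SARC-F score ≥4/10 and then muscle strength impairment), will benefit from a DXA exam". Under Follow-up – T1, "patient will once again benefit from CGA and sarcopenia assessment as described for T0", so eligibility for the scan is decided anew at each visit.

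The first step is the "SARC-F questionnaire (Strength, Assistance walking, Rise from a chair, Climb stairs, and Falls questionnaire". SARC-F is a screen and not part of the disease: the Abstract defines sarcopenia by low strength together with low muscle mass, and Data analysis takes an SMI below 7 kg/m² at either visit as proof.

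For incidence, the first secondary endpoint, the rule is "To evaluate incidence, enrollment (T0) will be considered as baseline and compared to T1 data". The same section says the secondary endpoints are compared between the two assessments for all patients. No sentence limits incidence to men whose T0 status was established.

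On strength testing there are two accounts. Screening and enrollment – T0 says "Muscle strength will be assessed for patient at risk of sarcopenia (impaired SARC-F"), and Primary endpoint agrees. Table 1 lists "Sarcopenia screening (SARC-F, Handgrip test and chair stand test") at T0 and T1 without that condition.

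**The concern.** The men with a known SMI at T0 and those with a known SMI at T1 are not the same set, and what separates them is a questionnaire score, not muscle. Take a man with low strength, low SMI and SARC-F below 4 at T0. He has no scan, so he cannot appear as a T0 case. If his SARC-F reaches 4 by T1 he is scanned, found to have low SMI, and looks like new sarcopenia with unchanged muscle.

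The score may also respond to treatment. SARC-F covers falls, assisted walking, rising and stairs. The Background lists altered physical function among the effects of ADT, and the Discussion gives this result of a preliminary study: "muscle disorders were present before initiation of ADT in older patients with prostate cancer and an increased risk of falls at the end of ADT". A change in who is scanned could therefore be mistaken for a change in muscle. The Abstract says the study intends to assess the specific effect of ADT on sarcopenia incidence or worsening, so the error bears on that conclusion. It is distinct from under-estimation of T0 prevalence, although the cause is the same.

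**Working it through.** **The plan's own figure.** The only calculated figure is the 95% interval width of 0.115 to 0.131 for 20–30% prevalence with 200 men (Sample size section). Exact Clopper-Pearson intervals for 40/200 and 60/200 have widths 0.1153 and 0.1313, so it reproduces. It uses all 200 men as denominator, which implies that unscanned men count as non-cases at T0. No size or precision is stated for incidence.

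**Inputs.** From the documents: N = 200; p = 0.25, the midpoint of 20–30%. Assumed, because the documents give no values: Se, the sensitivity of SARC-F ≥4 among truly sarcopenic men, 0.4 to 0.8; c, the share of men missed at T0 who cross SARC-F 4 by T1, 0.1 to 0.3; true onset of 10% among the 150 men not sarcopenic at T0; no loss to follow-up; detection at T1 the same as at T0.

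**Formulas.** Missed at T0 = 200·p·(1−Se). False incident = missed·c. Denominator (men not found sarcopenic at T0) = 200 − 200·p·Se. True new cases found = 150·0.10·Se.

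| | Se 0.4, c 0.3 | Se 0.6, c 0.2 | Se 0.8, c 0.1 |
|---|---|---|---|
| Missed at T0 | 30 | 20 | 10 |
| False incident | 9 | 4 | 1 |
| Denominator | 180 | 170 | 160 |
| Apparent incidence, no true onset | 9/180 = 5.0% | 4/170 = 2.4% | 1/160 = 0.6% |
| True new cases found, 10% onset (of 15) | 6 | 9 | 12 |
| Counted incidence, 10% onset | 15/180 = 8.3% | 13/170 = 7.6% | 13/160 = 8.1% |
| False share of counted cases | 9/15 = 60% | 4/13 = 31% | 1/13 = 8% |
| Counted incidence without the false cases | 6/180 = 3.3% | 9/170 = 5.3% | 12/160 = 7.5% |

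**Net direction.** Two errors oppose each other: false cases enter and true new cases are missed. They cancel at the true onset i that solves 150·i·Se + 50·(1−Se)·c = i·(200 − 50·Se), which gives i = 0.25·c, that is 7.5%, 5.0% and 2.5% in the three columns. Below that value counted incidence is too high; above it, too low.

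**If detection at T1 improves** because the score has moved, set T1 detection to Se + (1−Se)·c = 0.58, 0.68 and 0.82. Then 8.7, 10.2 and 12.3 true cases are found. Counted incidence is 17.7/180 = 9.8%, 14.2/170 = 8.4% and 13.3/160 = 8.3%, still below 10%. The false share becomes 51%, 28% and 8%.

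**Wider assumptions.** With p = 0.20–0.30, Se = 0.3–0.7 and c = 0.1–0.4, false incident cases run from 200·0.20·0.3·0.1 = 1.2 to 200·0.30·0.7·0.4 = 16.8. Apparent incidence with no true onset runs from 1.2/172 = 0.7% to 16.8/182 = 9.2%.

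**The case against.** A reader might infer that the error pushes incidence up and so mimics an ADT effect. The documents do not support that. At 10% true onset all three scenarios count fewer than 10%, because the same condition hides true new cases at T1; net inflation needs low true onset. This objection stands. What survives is contamination of the case count.

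A reader might also infer that the article expects SARC-F to worsen by T1. The preliminary falls finding concerns the end of ADT, whereas T1 is a year later, and falls is one of five components. A shift at T1 is plausible but not established.

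The coding of unscanned men for incidence is not stated, the full-population sentence covers only the primary endpoint, and an exact at-risk set is often left to a fuller document. This stands in part. But the article does fix the scan condition, its repetition at T1, T0 as baseline and a comparison in all patients. Treating unscanned men as non-cases is the reading that fits those rules and the 200-man denominator.

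Finally, chair stand evolution is already a secondary endpoint, so part of an unconditional comparison exists. That is true, but it is not named as the basis for a conclusion about ADT. It also depends on strength being tested in everyone, on which the article disagrees with itself.

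**Conclusion.** The point holds as a flaw in how incident cases are identified. Under the stated rules, men already sarcopenic but unscanned at T0 can be counted as new at T1 without any change in muscle. The mechanism rests on the text, together with the inference that unscanned men are carried as non-cases.

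The size does not rest on the text. The 1 to 9 false cases among 200, and the 8–60% false share at 10% true onset, depend on assumed sensitivity and crossing rates and are illustrative. The net direction of bias in the incidence rate is unknown. The affected men are those with low strength and low SMI but SARC-F below 4 at T0; if SMI below 7 kg/m² alone counts as proof, as one sentence in Data analysis says, the group is wider.

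**What to change.** 1. Reconcile Table 1, which schedules handgrip and chair stand for all at both visits, with Screening and enrollment – T0 and Primary endpoint, which make strength testing conditional on SARC-F. The steps below need strength results whatever the SARC-F score.

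2. In Data analysis, make incidence of impaired strength by the article's own cut-offs (handgrip below 27 kg or chair stand above 15 seconds), regardless of SARC-F, the T0–T1 comparison that supports any conclusion about ADT. The scan condition does not affect it.

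3. Report DXA-confirmed incidence only among men known to be negative at T0: normal strength at T0 (under the strength-plus-mass definition, which should be stated as the one in force) or T0 SMI of at least 7.0 kg/m². List the remaining men without a T0 diagnosis as T0 status unknown, outside numerator and denominator. State that the figure is a lower bound for that group, because the T1 condition still misses cases. The restriction cures the contamination, not the under-detection.

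The cost is a few sentences and one extra table, with no extra scan. The denominator for DXA-confirmed incidence shrinks and its interval widens, substantially so if strength is not tested in all men at T0.
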